**Methods:**

The present study is a randomized 3-group (BAI + SFAS vs. RT + SFAS vs. education control) trial with 525 EAs (175 per group; estimated 50% women and 50% African American) who report recent risky drinking and who are not students or graduates of 4-year colleges. Participants will have the option of completing the intervention sessions in person or via a secure video teleconference. Levels of drinking and alcohol-related problems will be evaluated at baseline and 1, 3, 6, and 12 months post-intervention. The primary hypothesis is that both BAI + SFAS and RT + SFAS participants will report significantly greater reductions in alcohol use and problems relative to education control participants, with no differences in outcomes between the two active treatment conditions.

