Two recent trials have examined BAIs that were adapted for non-student EAs recruited from communities in the USA. One study evaluated a single-session BAI that included personalized drinking feedback along with strategies for coping with stress and a discussion about participants’ vocational and educational aspirations (*N* = 164, ages 18–25) [22]. There were significant treatment effects on drinking but not alcohol problems at a 3-month follow-up and no drinking reductions at the 6- or 9-month follow-ups. Another study examined the short-term effects of a BAI for non-student EAs recruited from the community who did not plan to attend college (*N* = 167, ages 17–20) [23]. The single-session intervention included standard BAI content (personalized alcohol feedback delivered in a MI style) enhanced with a discussion of vocational and personal goals along with personalized feedback on time allocation to alcohol vs. other activity categories (cf. [24]). One- and three-month follow-up assessments revealed significant reductions in alcohol use and problems relative to a relaxation training control session. Treatment effects were partially mediated by increases in seeking alternatives to drinking [25].

Despite the promise of single session BAIs, effect sizes are generally small and there is a need to enhance these interventions with novel content to increase their efficacy with higher-risk EAs [21, 26]. The modest overall response may be due in part to the limited focus of BAIs, which generally target motivation to reduce drinking without addressing reasons for drinking (e.g., boredom, stress, lack of goals or future orientation) or providing alternative means of experiencing reward or reducing negative affect. Indeed, predictors of poor response to BAI include low levels of substance-free reinforcement, poor self-regulation/impulsivity, low future time orientation, and anxiety or depressive symptoms [24, 27–30].

Furthermore, help-seeking for alcohol-related interventions in EAs is low. One study found that only 23% of EAs were interested in responsible alcohol use, whereas > 45% expressed interest in programs focused on improving mood and planning for the future (careers, money, health, life balance) [31]. Thus, programs that address alcohol use indirectly in the context of an overall focus on wellness and enhancing mood and goal setting might have greater appeal and potential for dissemination than traditional brief alcohol interventions [21, 32].

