## The present study

The primary goal of the proposed study is to establish the efficacy of the BAI + SFAS and BAI + RT approaches, relative to an education only control condition, among high-risk community-dwelling EAs. The primary hypothesis is that at 1, 3, 6, and 12-month follow-ups both BAI + SFAS and RT + SFAS participants will report significantly greater reductions in alcohol use and alcohol problems relative to education control participants, with no differences in outcomes between the two active treatment conditions. A secondary hypothesis is that the predicted advantage for BAI + SFAS and RT + SFAS, relative to education control, will be mediated by changes in alcohol reinforcing efficacy, negative affective symptoms, and proportionate substance-related reinforcement. An additional secondary hypothesis is that the BAI + SFAS and the RT + SFAS conditions will be associated with greater reductions in alcohol demand, proportionate substance-related reinforcement, drug use, and negative affect than the control condition, with no differences in outcomes between the two active treatments.

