Participants will complete the baseline assessment via a web-based survey (either remotely or in the research laboratory) and will be asked to provide consent for the full study. Randomization will occur algorithmically immediately after the baseline assessment and will be stratified by gender and race/ethnicity. We will use an urn procedure to ensure baseline treatment group equivalence on past-month frequency of heavy drinking and drug use. Participants randomized to the education condition will receive the educational materials described below immediately after completing the assessment in the context of a 5-min discussion with a study clinician. Participants randomized to either of the active treatments will complete the first 50-min intervention session (BAI or RT) immediately after the baseline assessment. All participants will receive a $50 payment after completing this first phase, with an additional $10 bonus for attending session 1 on time to encourage attendance. Participants in the active treatment conditions will complete the 50-min SFAS 1 week later and will be compensated $40. Following the SFAS, participants will receive weekly, personally tailored text-message delivered support over the 4-week interval. Research staff will send participants appointment reminders by text message and email the day before their appointments. Participants who miss an appointment will be contacted by text message, phone call, and email up to three times per week until their appointment window closes. If we receive no response, we will contact the participant’s alternate contact person.

Research outcomes will be assessed via web-based surveys at 1 month, 3 months, 6 months, and 12 months after the baseline assessment (either remotely or in the research laboratory). See Table 1 for full schedule. Participants will receive a $40 payment for each of the follow-ups that they complete (maximum total study compensation is $260).

**Table 1 Tab1:** SPIRIT figure—schedule of enrollment, interventions, and assessments

	**Enrollment**	**Baseline assessment and randomization**				**Follow-up**			
			**Session 1**	**Session 2**	**Booster texts**				
**Timepoint**	***-t***_***1***_	***t***_***0***_	***t***_***0***_	***t***_***0***_** + *****1w***	***t***_***0***_** + *****2w–5w***	***t***_***0***_** + *****1 m***	***t***_***0***_** + *****3 m***	***t***_***0***_** + *****6 m***	***t***_***0***_** + *****12 m***

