### Preliminary analyses

Preliminary data analyses will include studies of patterns of missing data, dropout rates, therapist adherence, distributional properties of measures, and correlations among outcome measures. Outliers greater than 3.29 standard deviations (SDs) above or below the mean will be recoded to one unit above or below the highest or lowest nonoutlier value [55]. Second, we will use latent growth curve modeling (LGCM) to model trajectory shapes and assess growth rates over time and individual differences in the growth rates as a function of intervention. While the first approach will allow us to examine if and when the effects start to decay, the LGCM approach will inform us of the overall pattern of changes across time and allow us to test if the trajectory shapes differ between the control and the intervention conditions. With five measurement time points, we will be able to estimate trajectory shapes accurately beyond a straight linear trajectory. Linear and non-linear trajectory will be investigated to accurately model the trajectory shape supporting the hypotheses on intervention effects, as the outcomes may not decrease constantly as a function of time. As such, we will investigate the declining or plateauing measurement time points and model non-linear trajectory (e.g., piecewise, quadratic growth).

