### Intervention outcome analyses

Consistent with our previous approaches [24], evaluation of our intervention outcomes will occur via generalized linear mixed models with a negative binomial distribution and log link function (due to our expectation that the primary drinking outcomes will be skewed and zero-inflated). These models will (A) evaluate change in the primary drinking outcomes (drinks per week , past-month binge drinking, and alcohol-related problems) and (B) evaluate change in secondary outcomes (increases in proportionate reinforcement from substance-free activities and self-regulation, reductions in alcohol demand, drug use, and negative affect) across the four follow-up time points (1-, 3-, 6-, and 12-month) as a function of time and treatment condition. Time will be centered at the 1-month follow-up (time = 0 at 1-month follow-up) and baseline levels of the outcome will be included as a covariate. Random slope effects (i.e., time-by-treatment interactions) will be explored; however, our previous trial found they were not significant and were eliminated from the final reported models. Thus, we anticipate that final models will be estimated using a compound symmetry covariance matrix with random intercepts and linear effects of time. Age, gender, and ethnicity will be included as covariates due to their association with drinking level and the possibility of differential treatment response [56]. Models will be run with the following planned contrasts: active treatment versus education control, BAI + SFAS versus education control, RT + SFAS versus education control, and BAI + SFAS versus RT + SFAS. To test the hypothesis that no differences in outcomes will be found between the two active treatments, the two one-sided test (TOST) procedure for testing equivalence/noninferiority will be used [57]. Based on this approach, equivalence is established at the α significance level if a (1–2α) × 100% confidence interval for the difference in efficacies (RT + SFAS—BAI + SFAS) is contained within the equivalence margin or the interval (-δ, δ). This equivalence margin, *δ*, reflects the range of values for which treatments are “close enough” to be considered equivalent [57]. We have chosen the value *δ* = 1.12, for alcohol use, and *δ* = 0.82 problems, based on 75% the lower limit of a confidence interval of the difference between the BAI + SFAS against the assessment only in our previous trial [57–59].

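### The primary hypothesis is worded for four visits, but the planned contrasts name no visit, and what the treatment coefficient estimates depends on whether an interaction is kept

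*Protocol article*

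**What the plan says.** The section The present study puts the main claim at each follow-up, for drinking and for alcohol problems, with the education control as comparator: "The primary hypothesis is that at 1, 3, 6, and 12-month follow-ups both BAI + SFAS and RT + SFAS participants will report significantly greater reductions".

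Intervention outcome analyses fits one negative binomial mixed model with log link to the four follow-ups, with the baseline outcome as a covariate. On coding it says: "Time will be centered at the 1-month follow-up". On the interaction: "Random slope effects (i.e., time-by-treatment interactions) will be explored; however, our previous trial found they were not significant and were eliminated". The authors then anticipate random intercepts, compound symmetry and a linear time effect. Four contrasts follow (both active arms against control, each active arm against control, and the two active arms against each other). None is tied to a visit or to an average over visits. The equivalence test gives one margin for alcohol use (1.12) and one for problems (0.82), again with no visit or average named.

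Preliminary analyses adds latent growth curve models of trajectory shape, and says of another analysis: "While the first approach will allow us to examine if and when the effects start to decay". That section does not describe this other analysis.

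The time anchor also differs. The abstract has outcomes "evaluated at baseline and 1, 3, 6, and 12 months post-intervention"; the enrolment section and Table 1 count the visits from baseline.

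**The concern.** A hypothesis about four visits needs either a contrast at each visit or a statement that the claim is about an average. The article gives neither, and its anticipated model can deliver only one effect assumed equal at all visits.

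The sentence on random slopes makes this worse. A random slope is a variance: how much individuals differ in their rate of change. A time-by-treatment interaction is a fixed effect: how much the arms differ in their mean rate of change. Either can be present without the other. An analyst following the text could remove the fixed interaction because the slope variance was small, or because a test with limited power did not reject.

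At stake is how an effect that fades would be reported. The Background cites a single-session trial in non-student emerging adults with a drinking effect at 3 months and "no drinking reductions at the 6- or 9-month follow-ups". If a milder fade occurred here and the interaction was dropped, the report could present one effect through 12 months that is larger than the effect at 12 months.

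**Working it through.** **1. What the stated power refers to.** Inputs from Sample size and power: 175 per group, between-group d = 0.33 (drinks) and 0.32 (problems), alpha 0.05 (taken as two-sided), power 1.00/1.00. The attrition counts give 95 + 2×37 + 3×21 + 4×11 = 276 missing points. If all are at follow-up, that is 276/2100 = 13%, or about 152 per arm per visit. The within-person correlation r is not given; 0.4 to 0.7 is assumed. All calculations use a normal approximation on a standardised scale and ignore therapist clustering and the log link.

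- One visit, no covariate, 175 per arm: power 0.87/0.85. This does not give 1.00.
- Average of four visits adjusted for baseline, SE = √(2f/n) with f = (1+3r)/4 − r². At r = 0.4, f = 0.39, SE = √(0.78/175) = 0.0668, 0.33/0.0668 = 4.94, power 0.999. Over r = 0.4 to 0.7 and both effect sizes, power is 0.998 to 1.000 with 175 per arm and 0.994 to 1.000 with 152.

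So the stated 1.00 is reproduced by a pooled contrast. For one baseline-adjusted visit (factor 1 − r², d = 0.33) power is 0.92 to 0.99 with 175 per arm and 0.88 to 0.98 with 152. For significance at all four visits together it is 0.75 to 0.97 and 0.66 to 0.94.

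**2. What the coefficient means.** Write the treatment effect at month m as β + γ(m − 1), taking months as the time unit.

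- Interaction dropped (γ = 0): the effect is β at every visit. Centring has no influence on it.
- Interaction kept: β is the 1-month effect. The effects at 3, 6 and 12 months are β + 2γ, β + 5γ and β + 11γ. The plan lists none of these as a contrast.

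**3. A weak, gradual fade.** Assumed d = 0.25, 0.20, 0.10, 0.05 at 1, 3, 6 and 12 months. The mean time is 5.5 and the sum of squares is 20.25 + 6.25 + 0.25 + 42.25 = 69. Shown for r = 0.5 and 175 per arm:

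- Slope difference = (−4.5×0.25 − 2.5×0.20 + 0.5×0.10 + 6.5×0.05)/69 = −1.25/69 = −0.0181. SE = √(2(1−r)/(69n)) = √(1/12075) = 0.0091. Ratio 1.99, so the interaction is detected in 51% of trials.
- Average effect = 0.60/4 = 0.15. SE = √(2×0.375/175) = 0.0655. Ratio 2.29, significant in 63%.
- Under compound symmetry with equal numbers at each visit, the average and the slope are independent. Missed and significant: 0.49 × 0.63 = 0.31.
- At 12 months, SE = √(2×0.75/175) = 0.0926 and 0.05/0.0926 = 0.54, power 0.08.

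Over r = 0.4 to 0.6 and 152 to 175 per arm, missed and significant occurs in 27% to 34% of trials. At r = 0.7 it is 20% to 23%. The pooled 0.15 is three times the assumed 12-month effect.

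**4. Fades from the planning effect to zero.** Same formulas, r = 0.4 to 0.7:

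| Assumed effects | Case | Interaction detected | Pooled effect significant | Missed and significant |
|---|---|---|---|---|
| 0.33, 0.33, 0, 0 | r = 0.4, n = 152 | 88% | 63% | 7.7% |
| 0.33, 0.33, 0, 0 | r = 0.7, n = 175 | 99.7% | 82% | 0.2% |
| linear, 0.33 to 0 | r = 0.4, n = 152 | 80% | 78% | 15.5% |
| linear, 0.33 to 0 | r = 0.7, n = 175 | 99% | 93% | 1.0% |

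**The case against.** The other side has several good arguments. An effect pooled over follow-up is a legitimate target, and the stated power fits it. The authors have a reason to expect stability: their two-session predecessor reduced use and problems through 16 months, whereas the fading example is a single-session trial. The growth curve models are planned analyses of whether trajectories differ by arm, with piecewise and quadratic forms. The undescribed analysis of decay may have been lost in condensing a fuller protocol, and writing out visit contrasts is often left to an analysis plan.

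Much of this stands, and it rules out four stronger readings that a reader might infer:

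- That the plan has a rule to drop a non-significant interaction. It says the terms will be explored and reports what is anticipated from the earlier trial.
- That centring at 1 month and dropping the interaction compound each other. Centring matters only if the interaction stays, and without it the pooled contrast still uses the later data.
- That any fading effect would be reported as lasting to 12 months. Step 4 shows that a fade from d = 0.33 to zero is usually detected.
- That early recall or late booster texts spoil the 1-month visit. Session 1 takes place at baseline, so recall before the second session still follows the first, and the drinking measure asks about a typical week.

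What does not fall is the mismatch itself. The article fixes the time coding, the anticipated model and the contrasts, and these do not test the hypothesis as worded. The growth curve models test trajectory shape, not the group difference at each visit.

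**Conclusion.** The point holds as a mismatch between hypothesis and analysis, together with a technical error in the random-slope sentence. The plan does not say whether the primary claim is an average or an effect at each visit. Its treatment coefficient means one thing without the interaction and another with it, and no stated contrast covers 3, 6 or 12 months.

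The practical risk depends on the shape of any fade. It is material for weak, gradual fading (about 27% to 34% of trials at r = 0.4 to 0.6) and small to moderate for fades from the planning effect to zero (about 0.2% to 15.5% at r = 0.4 to 0.7). These figures rest on assumed effect patterns and correlations, two-sided 5% tests of a linear interaction, and removal of the term whenever it is not significant, which the authors anticipate but do not prescribe. If the effect is constant, the anticipated model is adequate and only the wording is at fault. The time-anchor discrepancy is minor.

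**What to change.** - Model follow-up visit as categorical and keep treatment-by-visit in the final model whatever its p-value.
- State the primary contrast, for example the average over the four visits, and report the four visit-specific contrasts from the same model. Limit a claim about any visit to that visit's contrast.
- State which contrast the equivalence test and its margins apply to.
- Decide on random slopes separately, and correct the sentence that equates them with the interaction.
- Describe the analysis that is meant to show decay, or delete the reference to it.
- Use one time anchor for follow-up in the abstract and the text.

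The cost is wording and a few more parameters. Visit-specific estimates will be less precise than a pooled one: with baseline adjustment and d = 0.33, single-visit power is 0.88 to 0.99 over the ranges above. Power for the average contrast is essentially unchanged, at 0.99 or more at the planning effects. The change should be made before outcome data are analysed by arm.

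### Two urn-balancing factors are missing from the stated covariates: baseline drug use in all three primary models, and baseline heavy-drinking frequency in the drinks-per-week and problems models

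*Protocol article*

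**What the plan says.** The enrollment and randomization section of the protocol article says that allocation "will be stratified by gender and race/ethnicity" and continues: "We will use an urn procedure to ensure baseline treatment group equivalence on past-month frequency of heavy drinking and drug use". Four factors therefore shape the allocation: gender, race/ethnicity, heavy-drinking frequency and drug use.

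The section Intervention outcome analyses specifies "generalized linear mixed models with a negative binomial distribution and log link function" for drinks per week, binge drinking in the past month and alcohol-related problems, over four follow-ups. On adjustment it says that "baseline levels of the outcome will be included as a covariate", and then "Age, gender, and ethnicity will be included as covariates due to their association with drinking level". No other covariate is named for these models.

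Table 1 shows that the Drug Use Questionnaire and the binge-drinking item are both collected at baseline. Drug use appears again under Exploratory moderation analyses, as a candidate moderator.

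**The concern.** Balancing allocation on a prognostic factor reduces the true variance of the treatment contrast. An analysis that leaves the factor out does not see that reduction. Its standard errors are then too large for the design that was run, and its intervals too wide. A robust (sandwich) standard error does not repair this, because it too takes no account of the forced balance.

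The article justifies its covariates by their association with drinking. On that reasoning, baseline heavy-drinking frequency belongs in the list at least as clearly as age does. The trial constrains allocation on two factors and then does not name them in the analysis.

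The cost is precision, not validity. Precision matters most for the comparison of the two active arms. There, success requires the whole confidence interval to lie within fixed margins of 1.12 for alcohol use and 0.82 for problems.

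**Working it through.** **Step 1: factors against covariates.**

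| Balancing factor | Drinks/week model | Binge model | Problems model |
|---|---|---|---|
| Gender | named | named | named |
| Race/ethnicity | as ethnicity | as ethnicity | as ethnicity |
| Heavy-drinking frequency | not named | near equivalent (own baseline) | not named |
| Drug use | not named | not named | not named |

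The binge match is close but not exact, because the binge item adds a two-hour window. Table 1 also lists the Drug Use Questionnaire among the primary outcomes. In a model for that outcome, baseline drug use would enter as its own baseline.

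**Step 2: the plan's power figure.** Sample size and power gives d = 0.33 (drinks) and 0.32 (problems), 175 per group, alpha 0.05 (taken as two-sided) and power 1.00/1.00. A single visit without adjustment has noncentrality d × √(175/2), which is 3.09 and 2.99, and power 0.870 and 0.849. For the mean of four follow-ups adjusted for baseline, the residual variance is (1+3ρ)/4 − ρ². The article gives no ρ. Assuming 0.5 to 0.7, the variance is 0.375 to 0.285 and power is 0.998 to 1.00. The stated figure is thus plausible for a repeated-measures analysis, although its simulation inputs are not shown.

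**Step 3: analytic cost.** If the omitted factors explain a share R² of the residual variance, the SE ratio is √(1−R²) and the equivalent sample size is 525/(1−R²).

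| Assumed R² | SE reduction | Extra participants on 525 | Single-visit power, d = 0.33 (0.870 without) |
|---|---|---|---|
| 1% | 0.5% | 5 | 0.873 |
| 2% | 1.0% | 11 | 0.877 |
| 5% | 2.5% | 28 | 0.886 |
| 10% | 5.1% | 58 | 0.902 |

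**Step 4: first simulation** (two arms of 175, one visit, negative binomial, 200 trials per setting, log baseline in both models, mean model SE). With urn-factor effects of 0.10 and 0.10 on the log rate per SD, the SE falls from 0.0840 to 0.0829, or 1.3%. With 0.20 and 0.15 it falls from 0.0872 to 0.0838, or 3.9%.

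**Step 5: second simulation** (three arms of 175, sum of four follow-ups, outliers beyond 3.29 SD pulled in as the article plans, 300 trials per setting, empirical SE). All parameters are assumed. The settings differ in the SD of the stable log drinking level and the SD of extra variation at follow-up.

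| Setting | Own baseline only | + race | + race, drug use | + race, drug use, binge frequency |
|---|---|---|---|---|
| 0.5, 0.3 | 0.0717 | 0.0713 | 0.0696 | 0.0686 |
| 0.5, 0.6 | 0.0986 | 0.0983 | 0.0965 | 0.0947 |
| 0.8, 0.3 | 0.0869 | 0.0869 | 0.0847 | 0.0775 |
| 0.8, 0.6 | 0.1095 | 0.1088 | 0.1078 | 0.1008 |

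Against own baseline only, race plus drug use cuts the SE by 1.6 to 2.9%, and adding binge frequency brings this to 4 to 11%. If race is already in the model, the relevant comparison is with the second column. Drug use then gives 0.9% (0.1078/0.1088) to 2.5% (0.0847/0.0869), and both urn factors give 3.7% (0.0947/0.0983) to 10.8% (0.0775/0.0869).

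**Step 6: equivalence.** The interval's half-width is proportional to the SE, so it shrinks by the same percentage. The article gives no SE for this contrast, so the effect on the chance of showing equivalence cannot be computed.

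**The case against.** The strongest reply is that little is at stake. Superiority power is stated as 1.00, no bias arises, and any error is conservative. Baseline weekly drinks already carries part of the information in heavy-drinking frequency. All of this stands for the superiority contrasts. It does not remove the benefit for the equivalence interval.

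The simulations are also simpler than the plan. Neither has clinician clustering, missing data or the urn itself. In the second, model SEs ran roughly 9 to 15% below the empirical ones, which is why empirical values are used there. Binge frequency was generated as a second noisy measure of the same drinking level, which favours a gain. The percentages are therefore indicative only.

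The article also keeps direct predictors of outcome as covariates under Exploratory moderation analyses. That rule depends on the data and belongs to the exploratory models, so it does not fix the primary adjustment set.

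A reader might infer two further faults that the article does not support:

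- **Race is omitted.** The text says ethnicity where the stratifier is race/ethnicity. But the models are described as following the previous trial, and Sample size and power says those models covaried race/ethnicity. This is wording to reconcile.
- **Baseline counts enter untransformed under the log link.** The article never states the scale, and an analysis plan may do so. In the second simulation, a log instead of a raw baseline changed the SE by between −0.8% and +0.6%.

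**Conclusion.** The point holds in a narrow form. As stated, the primary models omit baseline drug use throughout and baseline heavy-drinking frequency in two of three models, although allocation was balanced on both. The consequence is modestly wide intervals and no bias.

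The two urn factors are worth about 1 to 4% of the SE in one set of assumptions and about 4 to 11% in another. Most of the larger figure comes from heavy-drinking frequency. Both ranges rest on assumed associations, because the article gives no figure for how well these factors predict outcome beyond the outcome's own baseline.

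It would be wrong to conclude that the trial is underpowered for superiority on this account. This is an inexpensive improvement, most useful for the equivalence comparison.

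**What to change.** In Intervention outcome analyses, add baseline drug use and baseline heavy-drinking frequency as prespecified covariates in every primary outcome model, using the same variables and coding as the urn. In the binge model, state whether the outcome's own baseline serves as the heavy-drinking term. Replace ethnicity with the race/ethnicity variable used for stratification.

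The cost is a sentence in the plan and a few parameters in 525 participants. Both factors are already measured at baseline. The change should be fixed before any outcome data are analysed by arm.

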## Method

### Design overview

We will conduct a 3-group randomized controlled parallel group superiority (BAI + SFAS vs. education control; SFAS + RT vs. education control) and non-inferiority trial (BAI + SFAS vs. SFAS + RT). Participants will be 525 individuals between the ages of 18 and 29 years old (estimated 50% women and 50% Black) recruited from the Memphis community and via online recruitment efforts across the U.S. Eligible criteria are described below.

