## Sample size and power

We have focused our power analysis using Monte Carlo simulations [64] with population estimates and patterns of missingness from our previous trial [24]. These models from our previous trial used generalized mixed models which covaried gender and race/ethnicity, taking into account clustering by individual and therapist. Based on the Monte Carlo estimates comparing BAI + SFAS to control (within *d* = 0.83/0.71, between *d* = 0.33/0.32), we are proposing to recruit 525 subjects (175 per group) for the study. Assuming a similar pattern of attrition as our previous trial will result in *n* = 362 (69%) complete cases, *n* = 95 (18%) cases missing one data point; *n* = 37 (7%) cases missing two data points; *n* = 21 (4%) cases missing three data points; and *n* = 11 (2%) cases missing four data points. We calculated power via Monte Carlo simulations by determining the proportion of 1000 replications for which the null hypothesis that a parameter was equal to zero was rejected for each parameter at alpha = 0.05 (i.e., probability of rejecting the null hypothesis when it is false). This resulted in the following power estimates for typical drinks/problems: treatment effect of BAI + SFAS vs. control = 1.00/1.00; mediation via proportionate substance-free reinforcement = 0.90/0.99; mediation via negative affect = 0.85/0.93; mediation via alcohol demand: 1.00/1.00. While our proposed sample size would not be sufficient to detect very small effects, we believe such small effects are likely to have little clinical meaning in terms of the variables we are assessing in the present trial, and the necessary sample size to detect such effects would be very large (> 1000).

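### The equivalence margins of 1.12 and 0.82 read as differences in drinks and problems, but the planned log-link model yields a log rate ratio, and nothing connects the two scales

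*Protocol article*

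**What the plan says.** All references are to the protocol article.

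- **Model.** Intervention outcome analyses plans "generalized linear mixed models with a negative binomial distribution and log link function" for drinks per week, past-month binge drinking and alcohol-related problems, at four follow-ups with the baseline value as covariate.
- **Rule.** The same section applies two one-sided tests to the active arms: "equivalence is established at the α significance level" if the "confidence interval for the difference in efficacies (RT + SFAS—BAI + SFAS) is contained within the equivalence margin or the interval (-δ, δ"). The level α is given only as a symbol.
- **Margins.** They are "1.12, for alcohol use, and *δ* = 0.82 problems", and they are "based on 75% the lower limit of a confidence interval of the difference between the" BAI + SFAS and assessment-only arms of the earlier trial. The scale and confidence level of that earlier interval are not given.
- **Label.** Design overview describes a superiority trial against control "and non-inferiority trial" for BAI + SFAS against SFAS + RT.
- **Power.** Sample size and power gives 1.00/1.00 for BAI + SFAS against control, and figures for mediation. It gives none for the equivalence test. It adds: "While our proposed sample size would not be sufficient to detect very small effects".

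**The concern.** With a log link, the contrast between the two active arms is a log rate ratio. The margins do not look like log rate ratios: the text speaks of a difference in efficacies and attaches the word problems to 0.82. Nor are they ratio margins, because a ratio margin is not symmetric about zero and 0.82 lies below 1. The article names no step from the model contrast to a difference in drinks or B-YAACQ points.

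Two further points are unsettled. There are three primary drinking outcomes but two margins, and drinks per week and binge episodes per month have different units. One section calls the comparison non-inferiority, while another fixes a two-sided equivalence rule.

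Absence of a difference between the active arms is part of the primary hypothesis (The present study). If the scale stays open until the data are in, choosing it could decide the conclusion.

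**Working it through.** **Inputs from the article:** δ = 1.12 and 0.82; 175 per arm; between-group d = 0.33 (drinks) and 0.32 (problems); four follow-ups with baseline adjustment. **Assumed:** one-sided α = 0.05 (90% CI), the SDs, the within-person correlation r, and the SE of the log rate ratio. Attrition and therapist clustering are ignored, which favours the plan.

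**1. The plan's own power figure.** A two-sample formula with 175 per arm gives 0.87/0.85 for d = 0.33/0.32. The baseline-adjusted mean of four follow-ups has variance factor f = (1 + 3r)/4 − r². For r from 0.4 to 0.8 this gives power of 0.998 to 1.00. The stated 1.00 is therefore plausible, but it concerns treatment against control.

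**2. Which scale was meant?** The implied earlier lower limits are 1.12/0.75 = 1.49 and 0.82/0.75 = 1.09. As a log rate ratio, 1.49 would be exp(1.49), about a 4.5-fold difference at the lower limit. That is hard to square with d = 0.33, so outcome units are the more plausible intent.

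**3. Margins applied directly to the model contrast.**
- exp(±1.12) = 0.33 to 3.06; exp(±0.82) = 0.44 to 2.27.
- P(declared equivalent | true ratio R) ≈ Φ((δ − ln R)/SE − 1.645), because only the nearer bound matters here.

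| True ratio | Margin | SE 0.06 | SE 0.12 |
|---|---|---|---|
| 2, drinking | 1.12 | 1.00 | 0.97 |
| 2, problems | 0.82 | 0.68 | 0.28 |
| 3, drinking | 1.12 | 0.10 | 0.07 |

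For example, (1.12 − 0.693)/0.12 − 1.645 = 1.91, and Φ(1.91) = 0.97.

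**4. Margins in outcome units.** A lower limit cannot exceed its point estimate. If d uses the raw SD, δ is at most 0.75 × 0.33 = 0.25 SD for drinks and 0.75 × 0.32 = 0.24 SD for problems. Equivalently, the SD is at least 1.49/0.33 = 4.5 drinks and 1.09/0.32 = 3.4 problems.

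Power with no true difference is 2Φ(δ/SE − 1.645) − 1, floored at 0, where SE = SD × √f × √(2/175). The factor f = 0.385 arises at r = 0.3 or 0.45; the formula peaks at 0.391. At r = 0.7, f = 0.285; at r = 0.8, f = 0.21.

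| Drinks SD | f = 0.385 | r = 0.7 | r = 0.8 |
|---|---|---|---|
| 4.5 | 0.96 | – | – |
| 6 | 0.76 | – | – |
| 8 | 0.36 | 0.58 | 0.77 |
| 10 | 0.03 | 0.25 | 0.48 |
| 12 | 0 | – | – |

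For problems with f = 0.385, power is 0.95, 0.85, 0.59 and 0.32 at SD 3.4, 4, 5 and 6.

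**5. Non-inferiority or equivalence.** One-sided power is Φ(δ/SE − 1.645). For drinks at SD 10 and f = 0.385 it is 0.52, against 0.03 for the two-sided rule. The label therefore affects what the trial can show.

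**The case against.** The wording and the 4.5-fold check both point to outcome units, so a careful analyst would not put 1.12 on the log scale. Deriving a marginal difference from a log-link fit is a routine step that an article may leave to the full protocol or SAP. This has force, and it makes the log reading a risk rather than the likely intent. It does not remove the defect: the article itself fixes the model, the rule and the numbers, and as written they do not fit together.

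On the label, the analysis section does mention both equivalence and non-inferiority, its two-sided rule matches the hypothesis of no difference, and meeting that rule implies non-inferiority. That is right. What stays open is the conclusion when only one bound is met. The article also does not say that the alcohol-use margin covers binge episodes. The power section's pairing of typical drinks with problems suggests drinks per week, but this is not stated.

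Three stronger readings are tempting and not supported:
- **A threefold drinking difference would pass.** Threefold is the edge of the interval, for alcohol use only. A true threefold difference passes about 7% to 10% of the time; a doubling is the case that passes almost always.
- **175 per arm can hardly ever pass in outcome units.** This needs an SD and a correlation that the article does not give, and it is not shown for problems.
- **The trial should switch to one-sided non-inferiority.** That is a preference, and it would weaken the stated hypothesis. Superiority of each active arm over control is already hypothesised and contrasted.

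**Conclusion.** The concern holds as a mismatch between the margins and the model. Applied literally to the log-link contrast, the rule would call a true doubling of drinking equivalent with probability 0.97 to 1.00, and a doubling of problems with 0.28 to 0.68, given an assumed SE of 0.06 to 0.12. On the more plausible outcome-unit reading, δ is at most about 0.25 SD if d uses the raw SD. Power for drinks then runs from 0.96 to zero over assumed SDs of 4.5 to 12 with f = 0.385, and is higher with stronger within-person correlation. For problems it may be adequate. The article reports no power that would tell the reader which case applies. The same sentence can thus support a very lenient or a strict test of part of the primary hypothesis, so it should be settled before the outcomes are analysed.

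**What to change.** 1. State the unit of each margin, and give the earlier trial's confidence interval on that scale with its level.
2. Compute the contrast on the margin's scale: a model-standardised marginal difference in drinks per week and in B-YAACQ points, with a delta-method or bootstrap 90% CI. Alternatively, convert the margins to log rate ratios before testing. This needs a stated reference mean m, because log(1 ± 1.12/m) depends on m and is not symmetric.
3. Say that the alcohol-use margin applies to drinks per week. Give binge episodes their own margin or leave them out of the equivalence claim.
4. Reconcile Design overview with Intervention outcome analyses so that one hypothesis is tested.
5. Report the power of the two one-sided tests at 175 per arm, with the assumed SD and correlation.

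The cost is wording and one post-estimation step, with no extra participants. The stated power for this comparison may turn out less favourable than the 1.00 given for treatment against control.
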